### **3.4 Procedures and Screening Tests**

Tests that have been completed within 15 days *prior* to study entry can be reviewed and used to determine eligibility. (This will be done after subject consent.) In such a situation, entry evaluation tests do not have to be repeated.

#### **3.4.1 Study Evaluations at Entry (After Consent)**

- 1) Pregnancy test for female subjects who are of child bearing age
- 2) A clinical examination which will consist of a physical examination, including body temperature, pulse, blood pressure, respiratory rate, weight, signs and symptoms of tuberculosis
- 3) Medical history will be taken at enrollment to include any previous diagnoses of major organ systems
- 4) Sputum smear microscopy and TB culture

- 5) Medication history will include a complete history of any prescription or non-prescription medications taken, including actual or estimated start and stop dates; allergies to any medications and their formulations will be documented
- 6) A baseline Dynamic MRI scan
- 7) Sputum, urine, and blood collections for experimental tests (in Diagnostic/Laboratory Procedures)
- 8) EKG with recording of QTc interval

### 3.4.2 Diagnostic/Laboratory Procedures

#### ***Pregnancy Testing***

A 10 mL to 50 mL sample of urine will be collected for pregnancy testing at study entry and before each radiological imaging scan by commercial human chorionic gonadotropin ( $\beta$ -hCG) determination kit.

#### ***Mycobacterial Testing Procedures***

Within 2 weeks prior to surgery, approximately 3 mL to 30 mL of sputum will be collected in each of 1-3 sterile containers for AFB smear and culture (quantitative solid and liquid culture methods) and molecular testing. If subjects cannot expectorate, sputum may be obtained via induction with hypertonic saline as previously described [35]. A sputum booth, if available, will be used. In addition, if a prior culture for the subject has been archived, a sample of this isolate will be collected for molecular characterization.

AFB smears will be scored by the World Health Organization's (WHO) standard scale. (Laboratory services in tuberculosis control Part II, 1998. Microscopy Document WHO/TB 98.258. World Health Organization, Geneva, Switzerland.)

The bacterial isolate or sputum will be tested for species identification and the results of previously ordered DST tests may also be collected, recorded on the CRF in subject history, and banked and stored at ITRC or Yonsei University. These samples may be shipped to NIAID or UMDNJ for additional testing.

#### ***Dissection of nodules and cavities from resected lung tissue***

The dissection of resected tissue will follow established SOPs for determination of drug concentration in lesions and is described here briefly. All specimen collection tubes are prelabeled and weighed to speed the dissection process.

Prior to surgery, the CT will be reviewed by the pathologist and study team to form a dissection plan. Classes of tissue to be specifically collected are: 1) several regions of apparently normal tissue, 2) large caseous tuberculomas ( $\geq 0.5$  cm), 3) cavity contents, 4) cavity walls including fibrotic tissue layer 6) fibrotic granulomas, and 7) small nodules.

Each lesion collected will be classified, measured for size (length, thickness and depth will be recorded in order to calculate surface-to-volume ratio for PK modeling) and pH, weighed, and recorded on the dissection log describing the disposition of the tissue. All lesions will be divided in this priority as follows and described in the dissection SOP.

- 1) Tissue frozen in liquid nitrogen or dry ice for drug extraction

- 2) Tissue frozen in liquid nitrogen vapor on tissue trays for Imaging Mass Spectrometry and histology
- 3) Tissue in formalin fixation solution for histology
- 4) Any remaining tissue frozen in liquid nitrogen for back-up

All lesions will have at least one sample that may be examined by normal histology methods, including hematoxylin and eosin staining of either formalin fixed or frozen sections. In addition, sections will be stained for acid fast bacilli and CD31 or CD34 (vessels). Larger lesions (0.8 cm or greater) will provide tissue for assessment of bacterial burden, bacterial genome equivalence, bacterial gene expression, and lesion cellular content using standard laboratory procedures.

### ***Pharmacokinetic profiling of the study drugs***

Approximately 2 mL of blood will be collected in heparinized tubes at several time points between drug administration and vessel ligation, to measure the concentrations of the study drugs and evaluate drug absorption and systemic exposure. The timepoints will be (i) trough (immediately before drug administration), (ii) average  $C_{max}$  or peak (2 hours after drug administration), (iii) end of absorption (6h after drug administration), (iv) time of central line placement before anesthesia, and (v)  $T_0$  or time of ligation (L) of the vessels and bronchus. One additional blood sample may be collected at any time between drug administration and ligation with accurate recording of sampling time. The group of subjects receiving the study drugs 2 hours prior to surgery will only provide blood samples at trough, time of central line placement and  $T_0$ . The group of subjects receiving the study drugs four hours prior to surgery will provide blood samples at trough,  $C_{max}$ , time of central line placement and  $T_0$ . These procedures are outlined in the Study Schema. While exact timing of sampling can deviate from the recommended time points, as outlined in section 4.3, careful and accurate recording of the sampling time is the key to the success of the study.

Sputum will be collected before drug administration (1 mL or more) with accurate recording of each production time. Whenever possible, small sputum sample(s) (1 mL or more), spontaneously produced by subjects, will be obtained at any time between drug administration and surgery, with careful recording of the time of production. If these samples are not available due to lack of production, it will not be considered a failure in protocol execution. At the time of surgery, sputum will be sampled after endotracheal intubation using a suction catheter with a sputum trap. All samples should be stored in a below -70 °C freezer as quickly as possible after collection.

Urine will be collected from drug administration and throughout surgery, with accurate recording of time and volume. Creatinine and drug levels will be measured to estimate renal elimination throughout the study period as well as the true clearance of drugs that are minimally metabolized such as KM.

These blood, urine and sputum samples will be processed at ITRC or Yonsei University College of Medicine and approximately 0.5 to 1 mL of plasma and sputum will be transferred to and analyzed at UMDNJ to determine the concentrations of RIF, INH, PZA, KM, MXF, and other 2nd line drugs which the subjects will be taking concomitantly.

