### 3 Study Design and Methods

#### 3.1 Design

This is a single-dose pharmacokinetic study of 5 concomitant drugs where resected lung tissue will be recovered to determine and compare drug levels within plasma, sputum, healthy lung and pulmonary TB lesions over a 24h period. Comparison and modeling of the concentration-time profiles in plasma and lesions are used to infer permeability coefficients, exposure ratios and concentration gradients for five major 1st and 2nd line TB drugs: RIF, INH, PZA, KM and MXF. Subjects will be randomized to receive the 5 drugs at one time point, either at 2, 4, 8, 12 or 24h prior to surgery, or as close as practical to those times with careful recording of the time of administration. Enrollment will continue until evaluable tissues from 3 subjects have been processed at each assigned time point. Blood and sputum samples will be obtained just before drug administration (trough), and blood samples will also be obtained at 2h ( $C_{max}$ ) and 6h post-dosing or as practicable. Whenever possible, one additional blood and/or sputum sample will be obtained between drug dosing and surgery. Finally, blood will be collected at the time of central line placement and sputum at the time of intubation prior to surgery. The time of each blood draw and sputum collection will be recorded as carefully and accurately as possible. Urine will be systematically collected between the time of drug administration and surgery. The removed tissue will be dissected to separate lesion material from uninvolved lung. The location of each lesion within the lung lobes will be recorded. Each lesion will be measured and weighed, then further divided to perform the following analyses: determination of overall lesional drug concentrations by liquid chromatography-mass spectrometry (LCMS), imaging mass spectrometry and histopathology analyses to visualize 2D drug distribution within lesions. A pre-operative dynamic MRI scan (30-60 min duration) will be conducted one to two weeks prior to surgery to assess lesional perfusion and endothelial function. This procedure can be performed with most MRI machines in clinical use and this may be taken at a different site. A scan will be obtained before injection of the contrast agent (gadolinium). After the contrast agent is given, the subject will be scanned serially at several time points up to 8 minutes post-injection. The rate of gadolinium uptake and its retention properties will be determined using software. The entire scan will take about 45 minutes. A subject will participate in this study from entry (1 to 2 weeks prior to surgery), through surgery and for 48h post surgery.

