### Doses:

- Rifampicin (RIF) will be dosed orally at 600mg or 450mg for subjects under 50kg of bodyweight;
- Isoniazid (INH) will be dosed orally at 300mg;
- Pyrazinamide (PZA) will be dosed orally at 1.5g;
- Moxifloxacin (MXF) will be dosed orally at 400mg;
- Kanamycin (KM) will be dosed intramuscularly at 1g or 750mg for subjects under 50kg of bodyweight

The 5 groups of subjects are distinguished by the timing of the drug administration, determined by randomization. The timing will be one of 24, 12, 8, 4, and 2 hours prior to estimated vessel and bronchus ligation time, which takes place at varying times after the start of surgery, depending on the extent of adhesions between the pleural membrane and the lung lobes. These times may vary slightly due to constraints inherent to the surgical procedure. Therefore, the exact timing of vessel and bronchus ligation relative to drug administration will be recorded accurately. Ligation marks the time of isolation between tissue compartment and plasma compartment, and will therefore be used as the time post-dosing in the PK analysis.

We will allow the following deviations from assigned timing between drug administration and vessel ligation:

- minus 1h and plus 3h for the 2h group
- minus 2h and plus 4h for the 4h group
- minus 4h and plus 6h for the 8h group
- plus or minus 6h for the 12h group
- plus or minus 12h for the 24h group

In cases where these maximum deviations are exceeded, samples will be collected and analyzed for drug content, but the data will be marked as falling outside allowable time points. To compensate for these potential fall-outs, enrollment will continue until evaluable tissues from 3 subjects falling within the allowable window are obtained in each group. Two statistical analyses will be conducted, one including only those subjects in compliance with the protocol, and one including all subjects. Both sets of results will be interpreted in light of the cause(s) for delay.

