#### 24h to 2h prior to surgery

- Subject will receive the 5 study drugs **once**, as shown below.
- Doses:
  - RIF 600mg PO (450mg if <50kg);
  - INH 300mg PO
  - PZA 1.5g PO
  - KM 1g IM (750mg if <50kg)
  - MXF 400mg PO

**Drug administration:** 24, 12, 8, 4, or 2h (as randomized) prior to estimated vessel and bronchus ligation time, which takes place at varying times after the start of surgery, depending on the complexity of the surgical procedure (see section 4.3 above for allowable deviations from assigned time points). For subjects whose drug regimen already contains an aminoglycoside other than KM, this aminoglycoside will be substituted with KM, provided that the subject consented to the substitution.

**Blood sampling for PK:** just prior to drug administration, 2h post-dosing (except for group 5), 6h post-dosing (except for group 4 & 5), at anytime between drug dosing and surgery (optional), at the time of central line placement and at the time of vessel and bronchus ligation. While exact timing of sampling can deviate from the recommended time points, accurate recording of the sampling time is critical to the success of the study.

**Sputum sampling prior to surgery:** Sputum will be collected immediately before drug administration (1 mL or more) with accurate recording of each production time, only if the subject is productive. One additional sputum sample will be collected at any time between drug administration and surgery, with accurate recording of production time.

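### In the 2 h group the 2 h (peak) plasma draw is cancelled by assignment, although ligation up to 5 h after dosing counts as compliant

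*Protocol*

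**What the plan says.** Section 3.4.2 (Pharmacokinetic profiling of the study drugs) lists the plasma times and describes the second and third as average maximum "or peak (2 hours after drug administration), (iii) end of absorption (6h after drug administration"). It then exempts groups by label. The 2 h group "will only provide blood samples at trough, time of central line placement and" ligation. For the 4 h group it says "The group of subjects receiving the study drugs four hours prior to surgery will provide blood samples at trough", and goes on to list the 2 h maximum, central line placement and ligation.

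Section 3.3.2 (24h to 2h prior to surgery) gives the same exemptions by group number: "2h post-dosing (except for group 5), 6h post-dosing (except for group 4 & 5"). The text does not number the groups. Reading group 5 as the 2 h group and group 4 as the 4 h group follows from section 3.4.2 and from the order in which the times are listed.

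Section 3.3 (Doses) sets the tolerance at "minus 1h and plus 3h for the 2h group" and explains that ligation comes at varying times after surgery starts, "depending on the extent of adhesions between the pleural membrane and the lung lobes". It uses the actual ligation time in the PK analysis.

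Section 3.1 states that "blood samples will also be obtained at 2h" and 6 h, as practicable, without exempting any group. It asks for one further blood and/or sputum sample whenever possible. Section 3.4.2 permits one extra blood sample at any time before ligation.

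**The concern.** Leaving out the 2 h draw is sensible only if ligation happens near 2 h, because the ligation sample then doubles as the peak sample. The protocol's own window allows ligation 3 h later than that. The delay it describes arises after surgery has begun, so it moves the ligation sample but not the central-line sample, which is taken before anaesthesia. The two required post-dose samples can then lie on either side of the peak with nothing between them.

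In section 5.1 the plasma concentration from dosing onwards drives the lesion concentration, and permeability is inferred from that relation. A poorly described plasma curve therefore carries into the individual's exposure and absolute permeability. Only three evaluable subjects are planned per time point (section 3.3), so one such subject is a third of the group. A missed sample cannot be recovered later.

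**Working it through.** No figure in the plan depends on this point. The sample size of 15 in section 5.2 is unaffected.

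**1. Windows (section 3.3).**
- 2 h group: 2 − 1 = 1 h to 2 + 3 = 5 h.
- 4 h group, "minus 2h and plus 4h for the 4h group": 4 − 2 = 2 h to 4 + 4 = 8 h.

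**2. Required post-dose plasma samples against those windows.**

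| Group | Ligation window | Required post-dose samples | Cancelled draw that could still be taken |
|---|---|---|---|
| 2 h | 1–5 h | central line (no fixed time), ligation | 2 h draw, if ligation is after 2 h |
| 4 h | 2–8 h | 2 h, central line, ligation | 6 h draw, if ligation is after 6 h |

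The 6 h draw is no loss in the 2 h group, whose latest compliant ligation is 5 h. The 4 h group keeps its peak sample.

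**3. How far from the peak the required samples can be.** This is an illustration on assumed values: one-compartment oral model without lag, peak at 2 h, half-life 3 h.
- ke = ln 2 / 3 = 0.231 per h. Solving ln(ka/ke)/(ka − ke) = 2 gives ka = 0.924 per h.
- C(t) is proportional to exp(−ke·t) − exp(−ka·t): 0.341 at 0.75 h, 0.457 at 1.5 h, 0.472 at 2 h, 0.372 at 4 h, 0.305 at 5 h.
- Ligation at 5 h: 0.305/0.472 = 0.65 of the peak.
- Line at 0.75 h: 0.341/0.472 = 0.72. Line at 1.5 h: 0.457/0.472 = 0.97. Line at 4 h: 0.372/0.472 = 0.79.

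The highest required sample is thus 0.72, 0.97 or 0.79 of the peak, depending on when the line is placed. With peak time 1–3 h, half-life 2–6 h and the line 1–3 h before ligation, the range is 0.42–1.00 for ligation at 5 h and 0.82–1.00 for ligation at 2 h.

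**4. Error in individual plasma AUC0-5.** Assumed: ka 1/h with 70% CV, lag 0.4 h, half-life 3 h, 30% CV on volume and elimination rate, 15% assay error, individual Bayesian fit, 200–300 simulated subjects, ligation at 5 h. Error is the root mean square error of log AUC.

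| Line placed at | Lag between subjects | Without 2 h draw | With 2 h draw |
|---|---|---|---|
| 0.75 h | fixed | about 10.5% | about 8.6% |
| 0.75 h | log-SD 0.3 | 15% | 10% |
| 0.75 h | log-SD about 0.5 | 19–21% | 10–11% |
| 1.5 h | fixed to variable | about 10–13% | about 9% |

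**5. Effect on the permeability endpoints.** Absolute permeability follows the plasma error: about 12% versus 10% at the low end and 23% versus 11% at the high end. For relative permeability (nodule over healthy lung), with fixed lag and the line at 0.75 h, the median error without and with the draw is 4.0% versus 3.3% for assumed nodule/lung rates of 0.05/0.2 per h, and 19.5% versus 18.3% for 0.1/0.5 per h.

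**The case against.** The best defence is that the plan already softens the loss. Actual times are recorded and used, the other four groups supply 2 h plasma to a pooled model (section 5.2), and the extra sample could be taken at 2 h. In addition, section 3.4.2 describes this group as dosed 2 h before surgery. On that wording the central-line sample falls near 2 h and largely duplicates the omitted one. All of this stands as mitigation, but it does not close the gap. Section 3.3 counts the 2 h back from estimated ligation, so the line time is not established. The extra sample may be sputum under section 3.1 and has no set time. Pooling does not restore an individual's unsampled peak.

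A second defence is that the primary endpoint is a ratio of two tissues driven by the same plasma curve, so plasma error partly cancels. Step 5 supports this. A reader might infer that the gap distorts the RIF–KM comparison because RIF is oral and KM intramuscular. The documents give no basis for a material effect there.

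A reader might also infer that the 4 h group can miss its peak. It cannot under this rule, because it keeps the 2 h draw. It loses only the sample labelled end of absorption, and with ligation at 8 h that sample changes the AUC error only from 9% to 8%.

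Section 3.1 is a summary qualified by practicability, and the two detailed sections agree with each other. The difference in wording is worth aligning but is not a serious contradiction.

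**Conclusion.** The point holds for the 2 h group only, and it is minor. It concerns three of the 15 planned evaluable subjects, and among them only those ligated clearly after 2 h. In such a subject nothing required by the plan secures a plasma sample near the stated peak.

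The size rests on assumed pharmacokinetics and on a central-line time that the protocol does not give. The upper figure of about 21% needs both an early line (0.75 h) and roughly 50% variability in lag between subjects. With a fixed lag, or a line at 1.5 h, the gain is a few percentage points at most. The benefit is to individual exposure and absolute permeability, not to any appreciable degree to the primary comparison.

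**What to change.** In sections 3.3.2 and 3.4.2, replace the 2 h exemption by a rule on actual time: take the 2 h draw in any subject of the 2 h group whose vessels are not yet ligated 2 h after dosing. Alternatively, direct the extra blood sample that is already allowed to that time. Word section 3.1 to match. The 6 h exemptions need no change.

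The cost is a wording change and one additional timed 2 mL sample in theatre, in at most a few subjects. The other groups already have this draw scheduled. The sample size and the analysis stay as they are.

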### ***Determination of drug levels in uninvolved lung tissue and lesion homogenates by LCMS***

Aliquots of approximately 0.2g (0.1g to 0.25g with accurate recording of the weight to facilitate further processing) of lung and lesion material will be homogenized and processed according to the protocol provided by NITD. Homogenized samples will be mixed with a suitable volume of organic solvent based on indicated weight. The organic phase, containing small molecule drugs, will be evaporated to dryness. These lyophilized samples will be shipped to and analyzed by UMDNJ for the absolute quantification of study drug levels as well as concomitantly administered non-study drugs.

### ***Determination of drug distribution into normal lung tissue and lesions by imaging Mass Spectrometry***

Lesion and lung sections will be subjected to 3Mrad  $\gamma$ -irradiation to sterilize them prior to analysis by scanning MALDI-TOF. Slices of frozen tissue samples (~12-20  $\mu$ m thick) from each different lesion type will be mounted on flat metallic target plates. Histological analysis of alternating slices will direct the placement of matrix drops onto specific cells with high placement accuracy effected by a robotic micro-dispenser. Processing digital images of the spotted plate will provide relative locations of each matrix spot. These coordinates will then be transferred and registered to the mass spectrometer for automated data acquisition. The heterogeneity of drug distribution is visualized by the rate of change in brightness or color of the output file. The resolution (~50-500 $\mu$ M) is user-defined, within instrumentation or other limitations. Ion distribution is then superimposed onto the histology image, to co-register with the relative density and precise location of the analytes in the tissue/granuloma of interest.

### ***Detection of genetic polymorphisms of hepatic and enteric N-acetyltransferases (NAT1 and NAT2) and other polymorphisms related to TB drug metabolism***

Genetic analysis of the genes will be done by isolating DNA from whole blood or tissue. The human DNA will be amplified by using a series of specific primers that span the regions known to confer the difference in rapid and slow acetylators of INH, and Rifampicin metabolism (CYP3A4) as examples. The PCR products will be sequenced and the results compared with known sequences to classify the patients into categories.

### **3.4.3 Diagnostic Radiation**

There is no research radiation on this protocol. X-rays and CT scans will be performed as SOC at each hospital.

### **Sites responsible for data generation and analysis**

| Procedure                                                                                  | Responsible Site(s)                  | Location                                       |
|---------------------------------------------------------------------------------------------------|---------------------------------------------|-------------------------------------------------------|
| Microbiology (resistance detection by DST & molecular methods, AFB smear and culture, genotyping) | Yonsei University
ITRC
AMC, PNUH, NMC | Seoul, Korea
Seoul/Changwon, Korea
Busan, Korea |
| Histology (formalin)                                                                              | ITRC                                        | Seoul/Changwon, Korea                                 |

|                                                 |                                                                                |                    |
|-------------------------------------------------|--------------------------------------------------------------------------------|--------------------|
| Histology and IHC for vessels (frozen sections) | NIH                                                                            | Bethesda, MD       |
| Drug quantification by standard MS              | UMDNJ                                                                          | New Jersey         |
| 2D distribution of drugs by imaging MS          | Novartis Institute for Biomedical Research (dept of “Analytical Sciences”)     | Basel, Switzerland |
| Data analysis and modeling                      | Novartis Institute for Biomedical Research (Dept of “Modeling and Simulation”) | Basel, Switzerland |

